### Risk-benefit assessment

The study provides body-psychotherapeutic support for cancer patients. Essentially, we expect neither risks nor additional burdens to patients. However, in psychotherapy unwanted adverse effects might occur. Often it is difficult to distinguish between negative life events, undesirable developments of the disease, and side effects of psychotherapy [48]. Exposure to one’s own bodily disturbances could lead to increased short-term physical and mental distress. Nonetheless, we expect that potential distress can be dealt with directly during the intervention, given that trained, experienced psychotherapists conduct the BPT.

### Interventions

#### Group BPT intervention

The first author developed the intervention based on integrative body psychotherapy approaches [20, 28, 29], adapted to cancer patients and their needs and opted for group setting. Compared to individual therapy, group interventions may benefit from additional therapeutic factors and may have economic benefits [49, 50]. First experiences with group BPT for cancer patients were obtained from an initial group (6 patients), as described elsewhere [25]. The intervention is carried out in small groups within 6 sessions, 90 min each. The intended time frame for conducting all 6 sessions is 6–8 weeks (public holidays etc. included). The group BPT is provided as part of the outpatient service of University Hospital Basel and Cantonal Hospital Winterthur, using facilities from the Cancer Leagues Basel and Zürich in close proximity to the hospitals.

The 6 group BPT sessions will comprise the following topics: 1) general introduction, fostering of group cohesion and focus on bodily perception; 2) focus on bodily resources and grounding; 3) focus on closeness and distance regulation; 4) focus on social interactions and bodily impulses; 5) focus on embodied emotions; and 6) summary and transfer session. All sessions should proceed along the following phases: A) Opening: brief bodily exercise and exchange, preparing the specific topic of the session; B) Psycho-educational element and exercises triggering embodied experiences, focusing on the specific topic of the session with sharing (reflection and exchange of experiences during the exercise); C) Closure: résumé and farewell (see Table 2 and Grossert et al. [25]). Within this schedule, each session can be adapted to the composition of the current patient group and its respective needs. Thus, group processes can be addressed accordingly. In between sessions, patients are instructed to continue the exercises (supported by smartphone-based triggers, see below), making sure that tools, experiences, and strategies are transferred and integrated into their daily lives. To improve intervention adherence, participants are contacted, if they do not attend a group appointment without having given prior notice. Patients are informed that they can contact us at any time if they have any uncertainties or questions.

**Table 2 Tab2:** Content of interventions: Group body psychotherapy with cancer patients and smartphone based bodily interventions

	Content group body psychotherapy				Content audiofiles
Session	Topic	Opening including short feedback on the previous session	Introduction & Exercise including sharing 1) Introduction and Psychoeducation 2) Strategies/Exercise 3) Sharing of own experiences	Closure including perspective for the upcoming week	Smartphone based bodily interventions supporting transfer from group BPT sessions into daily live
Duration	In Total 90 min	15–20 min	50–65 min	10–15 min	randomly on 3 days a week 10–15 min
1.	Group cohesion and body perception and awareness	▪ Self-introduction ▪ Expectations and fears	1) - Reflection about bodily perception, body image, body disturbances and body work experience- Introduction of BPT terms 2) - Breath perception - Body awareness with BodyScan technique, supine position- Self - contact (hands on/off) 3) Reflection about own experience during the exercises	What can I take with me after this first contact in the group?	Body awareness with body scan technique
2.	Bodily resources and grounding/ anchoring	▪ Short body scan CEB ▪ Breath perception ▪ Feedback	1) - Body as a resource - Balance between distress and resources, bodily stress reaction, adapted [44] 2) - Body awareness with BodyScan technique, standing position - Foot work and anchoring with the focus on connection to stability, e.g. p97 [28]- Movement perception including mirroring 3) Reflection about own experience during the exercises	How to transfer exercise skills into daily life?	Anchoring/grounding with footwork using a small rubber ball
3.	Boundary awareness	▪ Short body scan CEB ▪ Anchoring exercise ▪ Feedback	1) Space and boundaries including importance of having the choice between own and shared space 2) Boundary awareness: - Lika Breathing technique, p37 [45] - Boundary awareness: exploring own space and own boundaries, p84 [28] 3) Reflection about own experience during the exercises	Transfer of boundary awareness into daily life experience.	Boundary awareness through Lika breathing technique
4.	Impulses and social/group interaction	▪ Short body scan CEB ▪ Lika breathing technique, p37 [45] ▪ Feedback	1) Social interactions and (body) impulses to get into/out of social interactions 2) – Body self-release techniques, adapted p209 [28] - Awareness of bodily perception and the nature of impulses - nonverbal contact Interaction with different body parts 3) Reflection about own experience during the exercises	How can I find a witness position being aware of perception and impulses? What do I need?	Relaxation through body self-release techniques
5.	Embodied emotions	▪ Short body scan CEB ▪ Anchoring exercise ▪ Feedback	1) Integration model of human experience, p26 [28] 2) - Mapping of feelings under the cancer disease and treatment - Focus on embodiment: body sculptures of emotions, adapted [46] 3) Reflection about own experience during the exercises	How to become aware of feelings and how to explore and share them in daily life?	Self-awareness through ‘four body zone’ exercise
6.	Summary	▪ Short body scan CEB ▪ Free choice of exercise repetition ▪ Feedback	1) Summary and open questions 2) Free choice of exercise repetition 3) Closing: Ritual “*being connected while continue on individual path*”	What would I take with me? What would I leave in this group/room? Evaluation	

*BPT* Body Psychotherapy, *CEB* Cognition, emotions, body perception

Group BPT is provided by three trained psychotherapists. In order to guarantee continuity within each group, one single therapist leads all 6 sessions of a specific group. Therapists have a professional background in terms of either a medical or psychological degree, followed by specialized training in integrative body psychotherapy (IBP; accredited by the Federation of Swiss Psychologists). Furthermore, they then receive training in the ‘group BPT for post-treatment cancer patients’ approach by the first author of the present study according to the specific manual which describes the group content in detail (manual not yet published, for an outline see Table 2.). At the beginning and end of completing a series of the six BPT session, mandatory peer consulting of the therapy is provided by the first author and then continuously ensured according to the needs of the group leader. In case the first author is conducting the group, continuous supervision of the therapy is provided by a senior body psychotherapist.

#### Smartphone-triggered interventions

The smartphone-triggered bodily interventions consist of brief BPT exercises aiming at supporting the transfer from the group BPT sessions into patients’ daily lives. Smartphone bodily interventions are triggered by short audio-clips, as described elsewhere [51]. The patients are asked to log into the system each day once. Then, they randomly receive either an audio-clip triggering a bodily intervention (3 times a week) or a control intervention (3 times a week). In case of technical difficulties, participants can contact the study team. The content of the bodily interventions is outlined in Table 2. The control interventions consist of 15 selected fairy tales all adapted approximately to the same length as the bodily interventions. The advantage of fairy tales is their universality and distance to the content of cancer diagnosis or its treatment. The smartphone-triggered bodily and control interventions are provided over a period of 5 consecutive weeks on 6 days per week, in parallel to the BPT sessions. Thus, each patient undergoes 15 bodily and 15 control interventions.

### Assignment of smartphone-triggered interventions

An independent party (Clinical Trial Unit (CTU) of the University Hospital Basel) generated the computer-generated random sequences, using the software R, allowing individual randomization of every training day of each trial participant to the bodily or control interventions (within-subject randomization). Randomization was blocked every six training days for each trial participant to ensure that during each training week, each subject is triggered for three bodily and three control interventions of the pre-specified 6 weekly exercises per trial participant over the 5 consecutive weeks. No further restrictions applied. The series of random sequences generated by CTU was provided to a collaborator, who sequentially linked each patient after enrolment with the next sequence on the list. Trial participants were blinded to randomization up until the moment at which the intervention was provided; Body psychotherapists (care providers) were blinded to randomization. Outcome assessment on each smartphone-based intervention day was conducted directly via smartphone, so outcome assessor blinding is not applicable.

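### The fixed 3:3 split in every six training days lets a participant who knows or infers the rule deduce late-block clips, so blinding until delivery is not guaranteed in the nested comparison

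*Protocol article*

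**What the plan says.** The section *Assignment of smartphone-triggered interventions* of the protocol article describes within-subject randomisation of training days. The block is constant: "Randomization was blocked every six training days for each trial participant". Its content is also constant, in that within each training week "each subject is triggered for three bodily and three control interventions". The section then adds: "No further restrictions applied". On masking it states, without qualification: "Trial participants were blinded to randomization up until the moment at which the intervention was provided".

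The section *Smartphone-triggered interventions* gives the order of events: "The patients are asked to log into the system each day once. Then, they randomly receive either an audio-clip triggering a bodily intervention". The comparator is easy to recognise: "The control interventions consist of 15 selected fairy tales all adapted approximately to the same length as the bodily interventions". The scheme runs for five weeks on six days a week.

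According to *Assessments*, presence, vitality and mood are self-rated before and after each clip. *Sample size estimation* assumes that 80% of daily interventions are completed. The smartphone comparison is listed among the secondary objectives in *Study aims and objectives*. It is the only randomised comparison in the trial, because the group therapy itself is evaluated without randomisation.

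**The concern.** Each participant receives both conditions and learns each allocation on hearing the clip. With a constant block of six split 3:3 and nothing further to disguise it, earlier clips carry information about later ones. After three of one kind, the rest of the block is fixed. The sixth day of a fully completed block is always fixed.

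A participant aware of the rule would then decide whether to log in, and give the pre-clip ratings, knowing which kind of clip comes next. Two routes to bias follow:

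- Anticipation could shift the pre-clip rating, from which the pre-to-post change is measured.
- Skipping an unwanted clip could make missing days depend on allocation. With 20% of days expected to be missed, there is room for this.

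Post-clip ratings cannot be masked in this comparison. Concealment before the clip is therefore the only masking it can have, and the article claims it in full.

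**Working it through.** **Inputs.** Block of 6 training days, 3 bodily and 3 control, no other restriction (*Assignment of smartphone-triggered interventions*). 5 weeks of 6 days (*Smartphone-triggered interventions*). Assumed participation 80%, and 96% seen in an earlier study (*Sample size estimation*).

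**The article's own figures.** 5 × 3 = 15 clips of each kind, and 30 × 0.80 = 24 completed interventions. Both agree with the text. The article gives no figure for predictability.

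**Step 1: all six days completed.** There are C(6,3) = 20 equally likely sequences. A day counts as determined if three clips of one kind have already been heard in the block. The best-guess column expects the kind heard less often so far, with a coin toss if the counts are equal.

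| Day | Determined | Best guess correct |
|---|---|---|
| 1 | 0 | 1/2 = 0.50 |
| 2 | 0 | 3/5 = 0.60 |
| 3 | 0 | 2/5 × 3/4 + 3/5 × 1/2 = 0.60 |
| 4 | 2/20 = 0.10 | 0.1 × 1 + 0.9 × 2/3 = 0.70 |
| 5 | 8/20 = 0.40 | 0.4 × 1 + 0.6 × 1/2 = 0.70 |
| 6 | 20/20 = 1.00 | 1.00 |
| Sum | 1.50 | 4.10 |

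Counting by sequence gives the same mean: 12 sequences end in one determined day, 6 in two and 2 in three, so (12 × 1 + 6 × 2 + 2 × 3)/20 = 1.5. The closed form 2m/(m + 1) with m = 3 also gives 1.5.

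- Determined: 1.5/6 = 25% of days, or 5 × 1.5 = 7.5 of 30 per participant.
- Correct guesses: 4.1/6 = 68.3%, against 50% under simple randomisation.

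**Step 2: missed days.** The article does not say what happens to the sequence when a day is missed, so both readings are shown.

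- *Sequence tied to calendar days, missed clips unseen.* A completed day is determined only if all three earlier clips of the exhausted kind were actually heard. If days are missed independently of each other and of allocation, the share is multiplied by the cube of the participation rate. At 80%: 0.8³ × 0.25 = 0.512 × 0.25 = 12.8% of completed days, or about 0.128 × 24 = 3.1 days per participant. At 96%: 0.96³ × 0.25 = 22.1%.
- *Sequence advances only with completed training days.* The 25% stands within each completed block, but skipping then mostly postpones a clip instead of removing it.

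**Step 3: what another block scheme would do.** A single 15:15 block over 30 days leaves 2 × 15/16 = 1.875 determined days, or 6.25%. Only C(15,3)²/C(30,6) = 207,025/593,775 = 35% of weeks would then contain exactly three bodily clips.

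**The case against.** The strongest reply is that these percentages describe someone who holds the 3:3 rule and keeps count. The article does not say that participants were told it. The blinding sentence can be read as procedural: nobody disclosed the allocation before delivery, and nothing in the article contradicts that. This stands in part. A reader might infer that participants did know the clip on a quarter of days, or that the nested result is biased. The document supports neither. It does describe a pattern repeated in five consecutive weeks with unmistakable clips and no step to hide it, so inference is open to participants and the sentence says more than the design secures.

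A second reply is that the 25% and the skipping argument do not belong to the same scenario. This stands. The full 25% requires completed blocks. Where skipping truly removes a clip, the calendar-tied reading applies and the share is about 13% at the planned participation. The range should be reported, not the upper figure alone.

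Third, no direction or size of bias from anticipation has been shown, and post-clip ratings are open whatever the block length. This also stands, and limits the claim to a possible bias.

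Fourth, the blocking serves a purpose: it secures three clips of each kind in each training week, and Table 2 pairs each of sessions 1 to 5 with its own audio exercise on three days a week. A reader might infer that the scheme must be replaced. The figures in step 3 do not support that: a longer block would reduce determined days but give up the intended weekly balance in about two thirds of weeks.

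**Conclusion.** The point holds in limited form. Constant 3:3 blocks of six and recognisable clips make the end of each fully completed block deducible for anyone who knows or infers the rule. The unqualified claim of blinding until delivery is therefore not guaranteed. The share of deducible days is 25% with all days completed, or about 13% of completed days at 80% participation if the sequence is tied to calendar days and missed clips stay unseen. The second figure assumes that days are missed independently of allocation.

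Influence on pre-clip ratings and on log-in is possible, not demonstrated. It concerns only the nested smartphone comparison, a secondary objective. The primary Body Image Scale analysis, the sample size and the power figures do not depend on it. The correction is still worth making, because this is the trial's only randomised contrast and the remedy is cheap.

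**What to change.** 1. Reword the blinding sentence: allocation was not disclosed before delivery, but concealment can be incomplete late in each block of six. State whether participants were told of the weekly split, and whether a missed day uses up its place in the sequence.
2. From the allocation list and the log-in record, flag each day whose type was already determined by clips that the participant had heard in that block.
3. Repeat the bodily-versus-control analysis without the flagged days, as a sensitivity analysis.
4. Compare log-in rates by allocation on determined and on undetermined days. A difference by allocation confined to the determined days would point to selective skipping.

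The cost is one flag, one log-in table and one extra analysis on up to about 25% fewer days, with some loss of precision. No new data are needed, so this works even if all sequences have been issued.

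Changing the block scheme for sequences not yet issued is optional. It would lower the share of determined days but give up the intended three bodily and three control clips per week, so the investigators would have to weigh one against the other.

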### Assessments

For all assessments, we apply validated instruments with good quality criteria. Sociodemographic variables are assessed at baseline (T0) only. All other constructs are assessed three times: at baseline after study enrollment (baseline assessment; T0), after the waiting period (pre-intervention assessment; T1), and after completion of the group BPT (post-intervention assessment; T2).

Within the group intervention, bodily disturbances, body mindfulness and group cohesion is evaluated weekly after each group BPT session. Experience of presence and experience of vitality and mood are additionally assessed pre- and post-smartphone-triggered interventions. Furthermore, therapist’s adherence to the manual is recorded with a respective checklist adapted to the session’s context. Table 3 gives an overview of outcome measures, assessment instruments, and time points.

**Table 3 Tab3:** Outcome measures, assessment instruments, and assessment time points

Measures	Assessment instruments	Baseline Assessment T0	Pre-Intervention Assessment T1	Weekly assessments after group BPT	Pre/Post smartphone-triggered intervention	Post-Intervention Assessment T2
Social demographics	Sociodemographic variables (sex, age, marital status, educational level, and job-related situation)	X				
Psychosocial health	Basic Documentation for Psycho-Oncology (PO-Bado)	X				
Performance status	Performance status score of the Eastern Cooperative Oncology Group (ECOG)	X				
Bodily disturbances	Body Image Scale (BIS)	X	X	X		X
Awareness of bodily changes due to the diagnosis and treatment	single item; VAS-A patient-assessed (range 0–10)	X	X			X
Distress caused by bodily changes	single item; VAS-B patient-assessed (range 0–10)	X	X			X
Body mindfulness	Body Mindfulness Questionnaire (BMQ)	X	X	X		X
Distress	National Comprehensive Cancer Network Distress Thermometer (DT)	X	X		X	X
Somatic Symptoms	Somatic Symptom Disorder-B Criteria Scale (SSD-12)	X	X			X
Quality of life	EORTC QLQ-C30	X	X			X
Vitality	36-Item Short Form Health Survey (SF-36) – Scale Vitality	X	X			X
Mental health	36-Item Short Form Health Survey (SF-36) – Scale Mental Health	X	X			X
Anxiety and depression	Hospital Anxiety and Depression Scale (HADS)	X	X			X
Suicidal tendency	Beck Depression Inventory (BDI-II), Item I: Suicidal tendency	X	X			X
Group cohesion	Group Climate Questionnaire – Short Form (GCQ-S)			X		X
Mood	Multidimensional Mood Questionnaire (MDMQ)				X	
Experience of presence	single item; VAS (range 0–10)				X	
Experience of vitality	single item; VAS (range 0–10)				X	
Therapist’s rating of patient’s bodily changes due to the diagnosis and treatment	Semi-standardized Interview single item; VAS-A therapist-assessed (range 0–10)	X				
Therapist’s rating of patient’s distress caused by bodily changes	Semi-standardized Interview single item; VAS-B therapist-assessed (range, 0–10)	X				
Motivation, previous experience, eligibility	Semi-standardized Interview	X				
Acceptance, treatment effect, potential for improvement, safety aspects	Semi-standardized Interview					X
Therapist’s adherence to the manual	Adapted checklist to session content (see Table 2.)			X		

*BPT* Body Psychotherapy, *EORTC QLQ-C30* European Organization for Research and Treatment of Cancer QLQ-C30, *VAS* Visual Analog Scale

The primary outcome, bodily disturbances, is assessed using the ‘Body Image Scale‘(BIS), which is a brief 10-item scale validated in cancer patients, showing sensitivity to change and high reliability (Cronbach’s alpha 0.93) and validity [52]. We translated this questionnaire from English into German according to the European Social Survey Translation Guidelines [53].

Secondary outcomes are assessed using the ‘Body Mindfulness Questionnaire’ (BMQ) with high internal consistencies (Cronbach’s alpha = 0.93 for “Experiencing Body Awareness” and 0.91 for “Appreciating Body Awareness”) [54], the ‘Somatic Symptom Disorder-B Criteria Scale‘(SSD-12) with high reliability (Cronbach’s alpha = 0.95) [55], the ‘Hospital Anxiety and Depression Scale’ (HADS, Cronbach’s alpha = 0.93 for “Anxiety” and 0.90 for “Depression”) [56, 57], and the ‘Multidimensional Mood Questionnaire‘(MDMQ; Cronbach’s alpha = 0.92) [58, 59]. Quality of life is assessed using the ‘European Organization for Research and Treatment of Cancer’ (EORTC QLQ-C30) questionnaire [60] with good reliability (Cronbach’s alpha = 0.82 for “Physical functioning”; 0.90 for “Role functioning”, 0.84 for “Emotional functioning”, 0.72 for “Cognitive functioning”, 0.86 for “Social functioning”, 0.86 for “Global Quality of Life, 0.84 for “Fatique”, 0.58 for “Nausea/vomiting”, and 0.86 for “Pain” [61]. And two scales (Vitality and Mental Health) of the ‘Short Form Health Survey ’ (SF-36, Cronbach’s alpha of 0.86 for Vitality and 0.84 for Mental Health) [62]. Additional information is collected using the ‘Basic Documentation for Psycho-Oncology’ (PO-Bado) [63], the ‘National Comprehensive Cancer Network Distress Thermometer‘(DT) [64, 65], and via the assessment of the performance status score of the Eastern Cooperative Oncology Group (ECOG) [66]. We apply single item VAS (0–10) to assess experience of presence and experience of vitality. The ‘Group Climate Questionnaire – Short Form‘(GCQ-S) [67] is used to assess group climate.

The baseline assessment includes a semi-standardized individual face-to-face interview (30–50 min). During this interview the group therapist addresses the most relevant key-issues regarding the intervention, as well as previous experiences, expectations, and concerns. Finally a semi-standardized individual face-to-face interview is conducted by the group therapist, to address treatment effect, effect mechanism, acceptance, and potential of improvement and safety aspects, as well as whether they would recommend participation in the intervention to other patients. The need for further psychological support is clarified in the final interview. If further psychological support is required, contact information of respective providers will be provided. The semi-structured interviews are audiotaped if participants provide respective informed consent. Afterwards, they are transcribed and evaluated according to Mayring [68] in order to investigate acceptance, treatment effects and mechanism, burden, and potential for improvement of the interventions. Exclusions, recruitment, and dropout rates will be recorded.

